### 2.5. Randomization and Blinding

Randomization will be performed after completion of baseline assessment and informed consent procedures. An independent researcher not involved in participant recruitment, intervention delivery, outcome assessment, or data analysis will generate the allocation sequence using the Sealed Envelope^TM^ (London, UK) online randomization tool, with a 1:1:1:1 allocation ratio.

Allocation concealment will be ensured using sealed, opaque, consecutively numbered envelopes prepared according to the generated sequence. The envelopes will be kept by an independent researcher and opened sequentially only after each participant has completed baseline assessments and provided written informed consent. Outcome assessors and data analysts will remain blinded to group allocation throughout the study.

Due to the nature of the intervention, participants and intervention providers cannot be blinded. Several measures will be implemented to minimize performance and detection bias. First, participants will be informed that they will be randomly assigned to one of several intervention approaches. However, they will not be provided with information regarding the specific study hypotheses or the intervention received by the other groups. Participants will be told that the study evaluates different approaches to improving physical function and urinary control in older women, without reference to the specific components assigned to each group. Second, exercise sessions for different intervention groups will be scheduled at separate time slots throughout the week, ensuring that participants from different groups do not share waiting areas, changing rooms, or common spaces during study activities. This separation of session schedules minimizes the risk of contamination and inadvertent unblinding. Third, participants randomized to the control group will receive their educational sessions in a separate setting and at different times from the exercise groups.

Given the multidimensional nature of the intervention, blinding of the intervention supervisor and the physiotherapist delivering the sessions is not possible. However, a standardized supervision checklist will be used to ensure intervention fidelity across sessions and minimize intervention-delivery drift.

A flow diagram describing the anticipated participant progression throughout screening, randomization, allocation, follow-up, and analysis phases is presented in Figure 1.

### 2.6. Interventions

The intervention will consist of 36 supervised multicomponent exercise sessions, and, for one study arm, six structured PSY sessions delivered over 18 weeks. Exercise sessions will be conducted twice weekly on non-consecutive days (55–60 min/session) and will target balance, power, strength, aerobic capacity, agility/coordination, and flexibility with progressive intensity. Sessions will be led by a physiotherapist specialized in geriatrics (five years of experience), with methodological oversight by a research supervisor using a standardized supervision checklist to ensure fidelity and safety.

Participants will be allocated to one of the four groups:-G1: (EX) PMT only.-G2: (EXVERB) EX plus verbal cues to facilitate PFM contractions during balance and strength exercises.-G3: (EXVERBPSY) EXVERB plus six structured PSY sessions delivered during the intervention period.-G4: (Control Group) Participants will receive four educational sessions (one per month, 45–60 min per session) focused on the prevention of geriatric syndromes and instructions to maintain their usual physical activity. The sessions will address topics related to breathing control, postural control, balance and fall prevention, and pelvic floor (PF) health. After study completion, control participants will be offered the opportunity to receive the intervention components not undertaken during the initial study phase.

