#### 2.6.2. General Aspects of the Exercise Protocol

Training will be delivered in indoor multipurpose rooms at the Faculty of Physiotherapy (University of Valencia) and the Cultural Center of Manises (Valencia, Spain). Prior to the intervention, participants allocated to the exercise intervention groups (EX, EXVERB, and EXVERBPSY) will complete two familiarization sessions over a two-week period to ensure the correct execution of the MTP, including movement technique, movement velocity, breathing patterns, and intensity regulation. Participants allocated to the EXVERB and EXVERBPSY groups will additionally complete two familiarization sessions as part of the PFM activation intervention. The first session will provide standardized educational information on PF anatomy and function, while the second session will include individualized instruction on correct PFM activation using biofeedback to enhance motor learning and control. Consequently, participants in the EX group will complete two familiarization sessions, whereas participants in the EXVERB and EXVERBPSY groups will complete four familiarization sessions in total. Participants allocated to the control group will not receive familiarization sessions.

Each session will follow a standardized structure based on American College of Sports Medicine (ACSM) recommendations [44]: (1) warm-up (≈5 min; joint mobility and low-intensity aerobic activity); (2) main phase (≈50 min; balance, power, strength, aerobic, agility/coordination, and flexibility components); and (3) cool-down (≈5 min; breathing and stretching). The duration assigned to each training component is approximate and includes the time required for exercise transitions, standardized verbal instructions, PFM cueing (when applicable), and the prescribed recovery periods between sets and exercises, thereby ensuring that the total duration of each supervised session remains within the planned 55–60 min. Training will be progressed according to specificity and progressive overload principles, aligned with evidence-based recommendations for fall prevention [45] and current clinical practice guidelines for PFM training in women [11,12,46].

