For the planned comparisons and multiplicity controls, when a significant group × time interaction is found for the primary endpoint (α = 0.05, unadjusted), the following five pre-specified pairwise contrasts will be conducted simultaneously within a single testing family, with sequential Holm–Bonferroni correction applied across all five contrasts at each time point [82]: EXVERBPSY vs. Control at T1; EXVERB vs. Control at T1; EX vs. Control at T1; EXVERBPSY vs. EXVERB at T1 and EXVERB vs. EX at T1. Contrasts 1–3 evaluate the superiority of each active intervention arm over the educational control, directly addressing H1. Contrasts 4–5 evaluate the incremental contribution of each sequentially added component—PSY support and PFM activation instructions, respectively—consistent with the additive design of the trial. The same family of five contrasts will be repeated at T2 to evaluate the persistence of effects at the 6-month follow-up, addressing H3. Between-group effect sizes will be reported as Cohen’s d with 95% confidence intervals for each planned pairwise contrast, and as partial eta-squared (η^2^p) with 95% confidence intervals for the overall group × time interaction F-test. The same family of planned pairwise comparisons will also be applied to secondary outcomes. For each outcome analysed, sequential Holm–Bonferroni correction will be applied across the five pre-specified pairwise contrasts at each time point to control the family-wise error rate within that outcome [82].

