To formally evaluate the dose–response pattern hypothesized in H2, a pre-specified linear trend analysis will be conducted using orthogonal polynomial contrasts applied to the group factor within the LMM framework. The four groups will be assigned contrast weights reflecting the sequential addition of intervention components and their expected incremental dose: Control = −3, EX = −1, EXVERB = +1, EXVERBPSY = +3. These weights correspond to the standard orthogonal polynomial contrast coefficients for four equally spaced ordered groups [40]. This analysis therefore assumes equally spaced incremental treatment effects across the four study arms and is intended to test the prespecified hypothesis of a monotonic additive dose–response trend, rather than implying that the additional intervention components are biologically or clinically equivalent. A statistically significant positive linear contrast at T1 will be interpreted as confirmatory evidence supporting a monotonic dose–response relationship across the additive intervention arms, consistent with H2. Results at T2 will be interpreted as exploratory, addressing the persistence of the dose–response pattern at follow-up. The effect size for the linear trend will be reported as r^2^contrast = Fcontrast/(Fcontrast + dferror). This analysis will be conducted for the primary endpoint and, as exploratory analyses, for the pre-specified secondary outcomes.

All secondary and exploratory outcomes will be analysed using the same LMM framework. Sequential Holm–Bonferroni correction will be applied across the five pre-specified pairwise contrasts for each secondary outcome, consistent with the primary analysis. However, no global family-wise error rate correction will be applied across secondary outcomes. Results will be presented with adjusted *p*-values for the planes pairwise comparisons, Cohen’s d effect sizes with 95% confidence intervals, and η^2^p for global F-tests. Findings from the prespecified secondary outcomes will be interpreted as supportive rather than confirmatory, whereas exploratory outcomes will be interpreted as hypothesis-generating.

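### Control is taught pelvic floor health and EX is not, so the Control-to-EX step of the H2 trend is a swap rather than an added component, and EXVERB vs EX tests a package rather than verbal cues

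*Protocol article*

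**What the plan says.** Section 2.6 defines the arms. Control attends four monthly sessions of 45–60 min, whose content is given as: "The sessions will address topics related to breathing control, postural control, balance and fall prevention, and pelvic floor (PF) health". EX is the power-based programme and nothing else. EXVERB is "EX plus verbal cues to facilitate PFM contractions during balance and strength exercises". EXVERBPSY adds six psychoeducational sessions to EXVERB.

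Section 2.6.2 adds detail that the arm list omits. All three exercise arms have two exercise familiarization sessions, and Control has none. Then: "Participants allocated to the EXVERB and EXVERBPSY groups will additionally complete two familiarization sessions as part of the PFM activation intervention". Of these two, "The first session will provide standardized educational information on PF anatomy and function"; the other gives "individualized instruction on correct PFM activation using biofeedback to enhance motor learning and control".

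Section 2.8.1 says of the pairwise tests that contrasts 1–3 compare each active arm with the educational control, and that "Contrasts 4–5 evaluate the incremental contribution of each sequentially added component—PSY support and PFM activation instructions, respectively—consistent with the additive design". For H2 it sets a linear trend with Control −3, EX −1, EXVERB +1 and EXVERBPSY +3, called "contrast weights reflecting the sequential addition of intervention components". A significant positive trend at T1 is to count as confirmatory support for a monotonic dose–response; the trend at T2 is exploratory.

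Limitation (i) in the Discussion concedes the imbalance in contact time. It also concedes that the control education, pelvic floor health included, may influence some outcomes.

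**The concern.** An additive trend needs each arm to contain the arm below it. On the stated content, pelvic floor education runs yes, no, yes, yes across Control, EX, EXVERB and EXVERBPSY. The first step of the ladder therefore removes something while adding exercise.

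The removed element is not neutral for this trial. The primary endpoint (Section 2.7.1) is the pressure of a maximal voluntary pelvic floor contraction, so teaching about the pelvic floor could plausibly act on it. If it does, exercise alone looks weaker than it is, and the H2 trend no longer measures what its description says.

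The second issue is separate and concerns labelling. The Abstract and Section 2.6 describe the EXVERB increment as verbal instructions or cues, whereas Section 2.6.2 shows that it also includes an education session and an individual biofeedback session. A positive EXVERB vs EX result could be reported as showing that cues alone work.

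**Working it through.** **Step 1. Stated components by arm (Sections 2.6 and 2.6.2).**

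| Component | Control | EX | EXVERB | EXVERBPSY |
|---|---|---|---|---|
| Exercise programme (36 sessions) | no | yes | yes | yes |
| Pelvic floor education | yes, one of several topics | none stated | yes, one session | yes, one session |
| Individual biofeedback instruction | no | no | yes | yes |
| Cued contractions | no | no | yes | yes |
| Psychoeducation (6 sessions) | no | no | no | yes |

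EX is contained in EXVERB, and EXVERB in EXVERBPSY. Control is not contained in EX. Control's education totals 4 × 45–60 min = 180–240 min over all its topics; the time spent on the pelvic floor is not given.

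**Step 2. Where an effect of control education enters.** Let e be the gain in the Control mean at T1, in SD units of the primary endpoint.

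- EX vs Control: μ(EX) − [μ(Control) + e], a shift of −e.
- Trend: −3[μ(Control) + e] − μ(EX) + μ(EXVERB) + 3μ(EXVERBPSY), a shift of −3e.
- EXVERB vs EX: Control does not appear, so the shift is 0.

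**Step 3. Illustration of size.** The protocol gives no value for e, so there is no figure of its own to reproduce. Inputs from Section 2.4: 120 randomized, 20% attrition, correlation 0.50. Hence n = 120 × 0.80 / 4 = 24 per arm, and the baseline-adjusted SD is √(1 − 0.50²) = 0.866. Two-sided α is 0.05 before Holm, and power ≈ Φ(effect/SE − 1.96).

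- EX vs Control: SE = 0.866 × √(2/24) = 0.25. Assumed true exercise effect: 0.5 SD.
- Trend: the squared weights sum to 9 + 1 + 1 + 9 = 20, so SE = 0.866 × √(20/24) = 0.791. Assumed means without control education: 0, 0.25, 0.50, 0.75, giving −0 − 0.25 + 0.50 + 2.25 = 2.50.

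The two illustrations use different assumed exercise effects and should be read separately.

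| e (assumed) | EX − Control | power | trend contrast | power |
|---|---|---|---|---|
| 0 | 0.50 | 0.52 | 2.50 | 0.89 |
| 0.1 | 0.40 | 0.36 | 2.20 | 0.79 |
| 0.2 | 0.30 | 0.22 | 1.90 | 0.67 |
| 0.3 | 0.20 | 0.12 | 1.60 | 0.53 |

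At e = 0.3 in the trend illustration, Control (0.30) lies above EX (0.25), so the order is not monotonic. The contrast is still −0.90 − 0.25 + 0.50 + 2.25 = 1.60, with power 0.53 to be declared positive. A significant trend could then be reported as monotonic although its first step is reversed.

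**Step 4. What contrast 5 estimates.** Subtracting the EX column from the EXVERB column leaves three items: the education session, the biofeedback session and the cued contractions. Section 2.6.2 counts the first two as part of the PFM activation intervention. The contrast is therefore valid for that package. It does not separate out the cues.

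**The case against.** The strongest reply is that the additive aim in Section 2.1 concerns what PFM instructions and psychoeducation contribute on top of the exercise programme, and that ladder is intact. Section 2.8.1 presents contrasts 1–3 as comparisons with an educational control, so EX vs Control answers the question it is said to answer. An active educational comparator is a legitimate pragmatic choice, Limitation (i) explains it, and its effect on EX vs Control runs toward the null. Section 2.8.1 also admits that equal spacing of the trend is an assumption. All of this stands. It does not rescue the trend: its weights cover all four arms, its description makes Control to EX an added component, and a positive result is to be read as confirmatory. Nor does Limitation (i) say that EX lacks the education.

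Three stronger readings are tempting, and the documents do not support them.

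- A reader might infer that none of the arms is nested. The three exercise arms are.
- A reader might infer that EX receives none of the topics taught to Control. EX has breathing work (Sections 2.6.2 and 2.6.8) and trains postural control (Section 2.6.4); only pelvic floor education is missing.
- A reader might infer that education also biases EXVERB vs EX upward, so that the two distortions add up. Control is not in that contrast, and the education given to EXVERB belongs to the intervention as Section 2.6.2 defines it. Its effect is part of the estimate, and becomes an error only if the result is credited to cues alone.

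**Conclusion.** The concern holds for two statements. First, the four-arm trend is described as adding components one at a time, and the arm definitions contradict this at the step from Control to EX. Any benefit of control education on the primary endpoint moves EX vs Control by −e and the trend by −3e, both toward the null when the true effects are positive. Second, EXVERB vs EX estimates a package that the Abstract and Section 2.6 name too narrowly.

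The size of e is unknown. The range 0 to 0.3 SD, the 0.5 SD exercise effect and the 0.25 SD steps are assumptions, and the powers are illustrations. The contradiction between the arm content and the wording of the trend does not depend on them. The pairwise comparisons remain valid for the contrasts actually made; what must change is the conclusion drawn from the trend and from contrast 5.

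**What to change.** - **Section 2.8.1, trend.** Remove the statement that Control to EX is an added component. Interpret the four-arm trend as being against an educational comparator, and confine the additive-component conclusion to EX, EXVERB and EXVERBPSY. No new test is needed: contrasts 4 and 5 already estimate those two steps, and their sum is EXVERBPSY minus EX.
- **Section 2.8.1, contrast 3.** Describe it as exercise versus education that includes pelvic floor health.
- **Abstract, Section 2.6 and Section 2.8.1, contrast 5.** Name the increment as the whole PFM package: education session, individual biofeedback session and cues.
- **Limitation (i).** State that EX lacks the pelvic floor education that the other three arms receive, and what this means for H2.

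These are wording changes. Their cost is a narrower H2 claim.

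If sessions have not started, giving EX the same standardized pelvic floor education is an option. It would make Control and EX more alike on this element and would take education out of contrast 5. It would also change the EX arm, so it would need ethics committee approval under Section 3.2. Changing the content of the control sessions is a debatable design choice and is not required to resolve this point.

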#### 2.6.1. Adherence and Intervention Fidelity

Adherence will be promoted through regular participant contact (telephone and/or in person), flexible scheduling, and reminder messages prior to assessments. Attendance of ≥80% of scheduled sessions will be considered adequate adherence. Attendance, progression variables (e.g., elastic-band resistance and grip width), and any adverse events (AE) will be recorded throughout the intervention. Reasons for discontinuation will be documented, and outcome data will be collected at each assessment time point whenever feasible, in accordance with the intention-to-treat principle.

#### 2.6.2. General Aspects of the Exercise Protocol

Training will be delivered in indoor multipurpose rooms at the Faculty of Physiotherapy (University of Valencia) and the Cultural Center of Manises (Valencia, Spain). Prior to the intervention, participants allocated to the exercise intervention groups (EX, EXVERB, and EXVERBPSY) will complete two familiarization sessions over a two-week period to ensure the correct execution of the MTP, including movement technique, movement velocity, breathing patterns, and intensity regulation. Participants allocated to the EXVERB and EXVERBPSY groups will additionally complete two familiarization sessions as part of the PFM activation intervention. The first session will provide standardized educational information on PF anatomy and function, while the second session will include individualized instruction on correct PFM activation using biofeedback to enhance motor learning and control. Consequently, participants in the EX group will complete two familiarization sessions, whereas participants in the EXVERB and EXVERBPSY groups will complete four familiarization sessions in total. Participants allocated to the control group will not receive familiarization sessions.

Each session will follow a standardized structure based on American College of Sports Medicine (ACSM) recommendations [44]: (1) warm-up (≈5 min; joint mobility and low-intensity aerobic activity); (2) main phase (≈50 min; balance, power, strength, aerobic, agility/coordination, and flexibility components); and (3) cool-down (≈5 min; breathing and stretching). The duration assigned to each training component is approximate and includes the time required for exercise transitions, standardized verbal instructions, PFM cueing (when applicable), and the prescribed recovery periods between sets and exercises, thereby ensuring that the total duration of each supervised session remains within the planned 55–60 min. Training will be progressed according to specificity and progressive overload principles, aligned with evidence-based recommendations for fall prevention [45] and current clinical practice guidelines for PFM training in women [11,12,46].

Exercise intensity will be adjusted weekly by modifying elastic band resistance (TheraBand^®^ CLX Loops), grip width, exercise duration, and postural demands according to the participant’s perceived exertion (OMNI-RES for elastic resistance) and their ability to complete the prescribed repetitions with correct technique [47]. The percentages presented in the intervention tables should be interpreted as approximate contextual descriptors of relative training intensity and do not correspond to directly measured one-repetition maximum (1RM) values for elastic resistance. Participants will perform exercises in a consistent order, alternating upper- and LL activities to manage fatigue [48]. Participants will be asked to maintain usual dietary and physical activity habits and to avoid other structured exercise programs during the study period.

Detailed progression of the multicomponent program across the 18-week intervention is provided in Table 2.

#### 2.6.3. Mobility/Warm-Up Component

Dynamic joint mobility exercises targeting the main joints involved in the training session (e.g., spine, shoulders, wrists, hips, knees, and ankles) will be performed, followed by low-intensity aerobic activity (40–55% of maximum heart rate), such as marching in place, light walking, or step-based movements. This warm-up aims to increase body temperature, enhance joint range of motion, and prepare the neuromuscular system for subsequent balance, strength, and power exercises. This warm-up protocol is consistent with current exercise prescription recommendations for older adults [44,49].

#### 2.6.4. Balance Training Component

The balance component will primarily target standing balance, with progressive increases in task difficulty by manipulating base of support, support surface (stable/unstable), visual input, center-of-mass position, and time under tension. Standing balance exercises were specifically selected because the intervention aims to improve functional postural control during weight-bearing activities, which are most closely associated with mobility limitations and falls in community-dwelling older adults. Safety will be ensured by positioning a chair or stable support adjacent to each participant when required. The balance progression by phase is described in Figure 2 and summarized in Table 3.

